
**Fig. 1 Fig1:**
[figure not shown]
Hunting and fear memory networks (adapted from [18])

Common psychological disorders among refugees and trauma-exposed populations include PTSD, depression, somatic symptoms, substance abuse, externalising/internalising symptoms in children and adolescents, and an increased propensity for aggressive behaviour [7, 11]. In Germany, it is estimated that approximately half of all newly arrived refugees meet the diagnostic criteria for at least one mental disorder [26]. Systematic reviews and meta-analyses estimated prevalence rates of ~30% for both PTSD and major depression diagnoses [27]. Increasing evidence further shows a heightened risk for involvement in crime (e.g. assault, street crime) in refugees [28]. In sum, the evidence suggests that refugees are at a particularly increased risk for developing the ‘classical’ trauma related sequelae such as PTSD, depression, delinquent/criminal behaviour and substance use disorders [27, 29, 30].

### Family relations and effects across generations

During periods of displacement (pre-flight, during flight, resettlement), the ability to meet the needs of all family members but especially those who need most protection – the children – is compromised. As this situation persists and periodically deteriorates, there is an elevated risk of substantial and pervasive ramifications of continuous and traumatic stress and mental ill health across generations [31, 32]. During recent years, studies have illuminated the trajectories from parental trauma and the related mental ill health to harsh parenting and its detrimental impact on offspring mental well-being (such as chronic depression and attachment disorders, anxiety, and others; e.g. [33–35]). For instance, in a case control study, Leys et al. [36] observed that Holocaust survivors with severe trauma-related symptoms exhibited family functioning patterns characterised by increased anxiety and reduced resilience compared to the control. The authors suggest that parental trauma has a harmful effect, impeding resilience and increasing intergenerational vulnerability to mental health disorders. Similarly, Peltonen et al. [37] highlighted the direct impact of maternal trauma on children’s emotional processing among a sample of 100 Syrian families (*N* = 212 children and *N* = 94 mothers) living in Turkey. Harsh disciplinary practices were associated with increased levels of anxiety and depressive symptoms in children. This highlights the far-reaching consequences of how parental trauma, compounded by displacement and resettlement stressors, impacts the mental health and the psychological integrity of the refugee offspring generation. In addition to these behavioural pathways of transmission, a related field of research suggests that violence experienced indirectly *in utero* by the mother, or directly during childhood or as adult, may lead to various severe and costly health and (epi)genetic (mal)adaptation in offspring [38–41]. In summary, the last decade has provided us with strong evidence to support the notion that violence breeds violence: organised violence spills over into the domestic, family and relationship spheres, setting in motion a powerful intergenerational cycle of violence that in turn undermines cohesion and trust [13, 42, 43].

### Social networks and marginalisation

The persistence of trauma related symptoms constitutes a significant impediment to the establishment and maintenance of relationships, while the concomitant marginalisation and discrimination exacerbate psychological symptoms. Taken together, the strength and density of social networks within host communities and the capacity of these communities to foster a supportive and inclusive environment has a significant impact on refugee’s mental well-being after resettlement [44, 45]. A number of cross-sectional studies with refugees have found an association between higher levels of psychological symptoms and lower levels of community participation. Namely, these studies have also highlighted related factors such as reduced social functioning, which includes communication difficulties and lack of social interest, and reduced social support [46–49]. A study of Sudanese refugees also found that those who perceived higher levels of social support had fewer symptoms of PTSD, anxiety and somatisation [50]. By providing a sense of belonging and mitigating feelings of isolation, social support can strengthen individuals' capacity to cope with the adverse effects of discrimination, thereby contributing to improved mental health outcomes [51]. In line with this, Ager and Strang [52] identify social connections as a core domain within their framework of refugee integration. The quality of these social connections can, for instance, significantly shape refugees’ perceptions and lived experiences of discrimination [53, 54]. However, while social support represents a critical protective factor, stand-alone support social support programmes are unlikely to sufficiently reduce traum-related symptoms [55–57].

### The economic costs of mental illness in refugees

Nightmares, intrusions and concentration difficulties, feelings of anxiety, anger, shame and other symptoms prevent refugees with poor mental health from functioning economically. In a prospective study, Dietrich et al. [58] found that mental health problems – especially when severe – affected the employment prospects for Syrian refugees living in Germany. Similarly, He et al. [59] conducted a cohort study in Sweden from 1960 to 1995 and demonstrated the increased vulnerability of the first generation of refugees to social and economic marginalisation. For instance, Straiton et al. [60] compared the sickness absence of migrants due to acute mental health problems with that of the native population over a 12-month period and showed that refugees had up to 7% more sick days than non-migrants. Consistent with this findings, Mastafa et al. [61] also found that mental illness increased broader societal costs (e.g. direct healthcare costs or indirect productivity costs). Therefore, the failure to provide effective intervention for refugees’ mental health will place a significant financial burden on tax-funded healthcare and social security systems.

### From past to current psychological treatment approaches for refugees

Common approaches applied for the treatment of trauma related disorders in refugees in high income countries have mainly included individual counselling or psychotherapy with ad hoc adaptation of modules from mainstream techniques such as cognitive behavioural or psychodynamic therapy to the psychological needs of the refugee client [62]. The enrolment rate of refugees into psychotherapeutic care is however very low [63]. Psychotherapists face various barriers to treating refugees, including linguistic, pragmatic, and structural considerations, as well as their own attitudes and competencies. Especially, refugees with predominant aggression rather than PTSD-related suffering would not be eligible due to an absence of diagnostic criteria. The authors also identified barriers to mental health care among refugees, namely, limited awareness for mental illness, fear of stigma, lack of knowledge of available services, and negative attitudes towards formal treatment [63]. For young male refugees with heightened levels of aggression, it is important to recognize that they may have learned to use aggressive traits as a coping mechanism for their trauma related suffering. This characteristic in and of itself may serve as a powerful deterrent to seeking counselling on the side of the refugee. Lending from Levesque’s process-oriented conceptual framework for access to healthcare [64], we recognize that strategic placement of psychotherapeutic services are to a large extent inadequate for refugees. Specifically, these services exhibit poor approachability, acceptability, availability, accommodation, affordability, and appropriateness. At the same time, refugees’ abilities to access care are also limited, including their ability to perceive (due to language barrier and cultural differences), seek (due to a new environment), reach (due to avoidance, scepticism, fear, practical issues), pay and engage (due to scepticism, norms, isolation). Recently, the inclusion of transcultural elements in psychotherapeutic approaches have gained prominence, but despite the increased availability of seminars on these topics (for e.g., in conferences, trainings, etc.) these efforts alone do not significantly improve the accessibility of psychotherapy services.

A special role within the mainstream psychotherapy approaches for refugees is played by Narrative Exposure Therapy (NET) [21, 65, 66]. About 25 years ago, in the context of organized violence, war and torture in Yugoslavia, Northern Uganda and Sri Lanka, a group of psychologists and researchers have developed NET [67]. The approach was grounded in culturally sensitive principles and universal neural mechanisms applicable to heterogeneous populations of refugees (and non-refugees), prioritising survivors' recovery needs and addressing multiple traumatisation [68–70]. With this approach, the developers broke with the then-prevailing taboo surrounding discussion of traumatic events, alongside prolonged exposure [71] and gave rise to a new era of trauma rehabilitation by giving victims a voice through testimony [68]. To allow for an efficient implementation in war-torn and resource-poor regions, NET is manualised, brief, and open access. Implementation by local counsellors without academic graduation in (clinical) psychology has become a pragmatic and successful *modus operandi* [72–77], including NET training-of-trainers schemes [77, 78]. Moreover, NET stands out for its ability to address severe and multiple traumatization across lifetime. While NET has been refined and adapted over the past decades, it has kept its outstanding procedural core structure and features, especially the theoretical framework which has been validated by numerous independent studies across various fields of psychotraumatology [14, 79–81]. Today, NET is considered one of the gold standard treatments of PTSD. The manual was translated in 12 languages and is used worldwide, universal applicability also allowed for the treatment if survivors in at risk populations, including survivors who are homeless or vulnerably housed [82, 83], who live in contexts of ongoing violence [84–87], or in psychiatric wards [88]. Clinical studies and randomised control trials (RCTs) with a broad population have confirmed significant treatment effects on posttraumatic stress symptom severity [89–93] as well as related problems such as depression [77, 94–96], borderline symptoms [94, 97, 98], somatization [99], physical health [70], pain symptoms [100], quality of life [101], guilt [72], shutdown dissociation and dissociative identity disorder [102, 103], aggression [86, 104], drug dependence [77], psychosis [105–107], disability [108], social dysfunction [86, 88, 104], chronic mental disorders [88, 109] and negative intergenerational effects [110]. Evaluations have further corroborated the benefits of NET by determining mechanisms of treatment effects on symptoms, such as improved top-down frontal cortical regulation of emotions and behaviour [111], improved immunological responses [99], and multiple epigenetic outcomes [112]. The benefits of NET not only appear shortly following completion, but also persist over time [90, 113]. The long-term effectiveness of NET deserves particular emphasis, and many (network) meta-analyses and reviews fail to capture this important aspect. NET was adapted for the special needs of children and adolescents [114, 115], perpetrators [84, 86, 116], communities [85, 117, 118] and online delivery [119, 120], and it is applicable and effective in a wide variety of samples without the need for further adaptation (see Box 1).

**Table Taba:** Box 1

The mentioned studies have involved individuals of the following populations:
Refugees/migrants · torture survivors · low and middle income countries · post-conflict · gang members · ex-combatants · soldiers · survivors of gender based violence · individuals with diagnosis for borderline personality disorder · complex trauma · dissociative identity disorder · psychotic symptoms · other severe mental illness · pregnant woman · children with neurodevelopmental disabilities · elderly adults · individuals in insecure living conditions and ongoing violence · children and adolescents · gender diverse and intersectional groups / LGBTQ+ · individuals with intellectual disabilities · homeless persons or vulnerably housed · indigenous · survivors or trafficking

The overarching objective of this project is to pick up the key elements of this extensive knowledge gained from diverse countries of origin of refugees and integrate these into the German mental health system. To this end, we introduce a stepped-care trauma rehabilitation programme [121, 122] expanding the system with a peer counsellor component called *‘NAT counselling intervention’*, which integrates a screen-to-counsel approach for refugees residing in temporary accommodation in Germany (see Fig. 2). The specific goals of the ‘NAT counselling intervention’ are: (1) to invite asylum seekers to participate in a screening session conducted by a trained and assigned peer NAT counsellor with a similar cultural background, to assess potential psychological sequelae of traumatic events; the results of the screening are evaluated, and the client is categorized based on the logic of a traffic light system: red, yellow, or green and then referred to appropriate help, based on the severity of score identified by the 15-item Refugee Health Screener [123], a validated tool with excellent psychometric properties to screen for trauma related symptoms and probable diagnoses [124]; (2a) to deliver a specific counselling intervention called *‘NAT Narrative Trauma Work’* [125], adapted from NET and delivered by counsellors, for refugees with subclinical levels of symptoms (‘yellow’ group; RHS score of 13–36); and (2b) to facilitate the referral of refugees with a high likelihood of trauma related disorders (‘red’ group’; RHS score of ≥ 37) to a licensed psychotherapist^1^ for appropriate treatment, or (2c) to monitor and reevaluate cases with low symptoms; (3) follow-up; and (4) monitor psychological resources that enable individuals to participate in the community and society (‘well-being monitor’).

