**Methods:**

To assess the effect of NAT, we will apply a quasi-experimental parallel group study with a natural waiting list control group (regression discontinuity design). Follow-up assessments will be conducted continuously up to 12 months later, in person and online. The outcomes of the study will include symptoms of depression, anxiety and posttraumatic stress, using the Refugee Health Screener (RHS-15, primary outcome). The study will also assess social and economic integration, and resilience, as well as successful application of the NAT counselling intervention, amongst other measures. Cost-effectiveness and sustainability will be assessed for the overall programme. Sustainability will be measured on the basis of counsellor participation and satisfaction using a mixed methods approach. The study will be conducted at various selected sites in southwest Germany.

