All steps of the NAT counselling intervention are carried out by trained counsellors under the supervision of NET experts (from vivo international e.V. and the University of Konstanz) or otherwise trained licensed psychotherapists. The NAT counsellors themselves are peers in terms of their cultural and migrant background and therefore have similar biographical experiences, moreover are familiar with and well-integrated into German culture and have good language skills (mother tongue and German) and strong social skills. It is recognised that conditions in the countries of origin vary and therefore the requirements for recruitment and inclusion of counsellors in the project programme have not been rigidly defined but are rather based on the real-world setting. However, high motivation, impartiality and strong integrative and social skills are prerequisites for participation in the NAT training programme. Exclusion criteria for counsellors include: suffering from a mental illness, holding extreme or radical religious or ideological views, have insufficient language skills or illiteracy in German. In addition, we provide a screening for PTSD symptoms in an initial session using the PTSD Checklist for DSM-5 [127, 128]. Following this assessment, participants are provided with an individualised information session on the potential psychological impact of the project and supported to make their own decision as to whether or not they are ready to train and work as a counsellor and to undergo counselling themselves. Due to the sensitive nature of this personal health information, no written records are made or kept.

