## Interventions

### Explanation for the choice of comparators

In this naturalistic study, the following potential comparators to NAT (treatment condition) evolve: (1) NAT clients awaiting treatment; (2) clients with clinically relevant symptoms who are either (2a) waiting for psychotherapy or (2b) receiving psychotherapy; (3) clients without symptoms waiting for follow-up; and (4) clients before vs. after NAT (individual trajectories of symptom development, Table 1).

**Table 1 Tab1:** Constellation of comparators

Treatment condition	Control condition	Limitation	Mitigation
[1] NAT	Awaiting NAT (RHS 13–36)	Reduced follow-up time points for those who wait for treatment; unknown N	-
[2] NAT	[2a] PT waiting [2b] PT receiving	Clients might still wait but may have started, or already finished PT; higher symptoms of the control group at baseline	Statistical control for the number of treatment sessions, use of the RDD
[3] NAT	Watchful waiting (RHS < 13)	Lower symptoms of the control group at baseline, low symptom levels generally	Evaluate number of clients who present with improving vs. deteriorating symptoms rather than
[4] After NAT	Before NAT	Within subject comparison; potential confounding factors	-

Note: RHS-15 = 15 item Refugee Health Screener with a sum score indicating symptom severity; PT = Psychotherapeutic sessions provided by a licensed Psychotherapist. Threshold to clinical relevance is suggested for ≥37. Watchful waiting is indicated for clients with ≤12 points

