**Moderate stress (RHS 13–36 or no acute danger to self or others)**
Individuals in this category are unlikely to meet diagnostic criteria for trauma related disorders but are expected to have experienced trauma exposure. To protect these individuals from developing a trauma related disorder in the future, NAT counsellors will continue to provide step 2, 3 and 4 of NAT. In NAT, the counsellor guides the client in creating a chronological narrative of their life, focusing on traumatic experiences while also incorporating significant positive life events. This process allows clients to contextualise their network of sensory, cognitive, and affective memories of the past, thereby addressing the trauma memory structures. Moreover, NAT enables clients to reflect on their entire life journey, fostering a sense of personal identity and agency in the present ‘here and now’ and a positive projection of the client’s individual future. This approach conveys a notion of integration and a sense of achievement regarding their life in Germany. Implementing peer counsellors at this point leverages the ability to learn from role models while reducing cultural barriers such as language or varying interaction styles. Licensed psychotherapists and experts in psychotraumatology supervise the process, ensuring the correct application of the NAT intervention. In the event of worsening symptoms, a referral is being discussed based on a carefully developed protocol and set of criteria.

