## Statistical methods

### Statistical methods for primary and secondary outcomes

#### Feasibility assessment

[1a-d] Descriptive statistics (frequencies, percentages, means, standard deviations) will be used to assess the feasibility of NAT and the NAT counselling intervention programme in general (Table 4). These quantitative measures will be complemented by qualitative data from focus groups conducted with NAT counsellors as participants. The focus groups will explore perspectives on the need for the programme, areas for improvement, perceived effectiveness, barriers and facilitators to implementation, participants’ experiences and suggestions for improvement (Table 4). Content thematic analysis will be used to analyse the qualitative data to provide a comprehensive understanding of the feasibility and potential for improvement of the programme, using Nvivo software for data analysis.

**Table 4 Tab4:** Summarises the research questions and associated specific hypotheses

Research question	Alternative hypothesis	Null hypothesis	Ref.
Is the overall programme **sustainable**?	The majority ( > 50%) of refugees who leave the temporary accommodation have taken part in the project.	The minority ( < 50%) of refugees who leave the temporary accommodation have taken part in the project.	1a
	The programme is evaluated positively by stakeholders (refugees, counsellors, social workers).	The programme is evaluated negatively by stakeholders (refugees, counsellors, social workers) regarding issues that cannot be improved.	1b
	Recommendation to indicated treatment is followed by more than 50% of refugees.	Recommendation to indicated treatment is not followed by more than 50% of refugees.	1c
	The majority ( > 50%) of trained counsellor perform the screening and provide the intervention.	Only a minority ( < 50%) of trained counsellors perform the screening and provide the intervention.	1d
Is NAT **effective** (prevention)?	The number of participants with subclinical symptom levels at baseline who require specialised psychotherapeutic treatment after 6–9 months is lower in participants who received NAT than in the control group.	The number of participants with subclinical symptom levels at baseline who require specialised psychotherapeutic treatment after 6–9 months is equal in participants who receive the adapted NET compared to the control group.	2a

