	The number of participants with subclinical symptom levels at baseline who do not require treatment after 6–9 months is higher in participants who received NAT than in the control group.	The number of participants with subclinical symptom levels at baseline who do not require treatment after 6–9 months is equal in participants who receive the adapted NET compared to the control group.	2b
Is NAT **effective** (symptom reduction)?	Symptom reduction in participants with subclinical symptom levels is stronger in participants receiving NAT than in the control group (see Table 1).	Symptom reduction in participants with subclinical symptom levels is the same in participants receiving NAT compared to the control group (see Table 1).	3
[4] Is the programme generally cost-**effective**?	The financial costs of the NAT counselling intervention are lower than those of other interventions.	The financial cost of the NAT counselling intervention is equal to or higher than other interventions.	4

[2a+b] Chi-squared tests will be used to compare the frequency of participants with subclinical symptom levels requiring more/less intensive treatment during the programme. Logistic regression analysis will be considered to estimate the odds of refugees with or without NAT requiring more/less intensive treatment (Table 4).

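### NAT versus awaiting NAT is a non-randomised contrast within one RHS band, yet hypotheses 2a/2b are tested with an unadjusted chi-squared test, although access to NAT may differ by language or culture group

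*Protocol article*

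**What the plan says.** The abstract describes "a quasi-experimental parallel group study with a natural waiting list control group". In Table 1 (Explanation for the choice of comparators), row [1] sets NAT against clients awaiting NAT with RHS 13–36. The limitation listed there is "Reduced follow-up time points for those who wait for treatment; unknown N", and the mitigation cell holds only a dash. Row [2] offers statistical control and the RDD, and row [4] at least names possible confounding. Row [1] does neither.

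Hypothesis 2a (Table 4) reads: "The number of participants with subclinical symptom levels at baseline who require specialised psychotherapeutic treatment after 6–9 months is lower" in those who received NAT than in controls. Hypothesis 2b is the mirror image for clients who no longer need treatment. For both, the Statistical methods state: "Chi-squared tests will be used to compare the frequency of participants with subclinical symptom levels requiring more/less intensive treatment during the programme". Logistic regression is only to be considered, and no covariate is named.

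On delivery, programme goal 1 (at the end of the section on past and current treatment approaches) provides for "a screening session conducted by a trained and assigned peer NAT counsellor with a similar cultural background". Under Eligibility criteria, "The NAT counsellors themselves are peers in terms of their cultural and migrant background", and they "have good language skills (mother tongue and German) and strong social skills". The moderate-stress entry of Table 2 credits peer delivery of NAT itself with "reducing cultural barriers such as language or varying interaction styles".

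**The concern.** Hypotheses 2a/2b concern clients who are subclinical at baseline, which the article equates with RHS 13–36. The only comparator in that band is the awaiting-NAT group. Whatever decides who starts and who waits is therefore a potential confounder, and the article does not say what that is.

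The text does point to one plausible factor. Counsellors work in their mother tongue and share the client's cultural background, and their recruitment is left to real-world conditions. Capacity may thus be uneven across language or culture groups, so that treated and waiting clients come from these groups in different proportions. If the groups also differ in their risk of needing specialist care at 6–9 months, an unadjusted comparison mixes that difference with any effect of NAT. The error can flatter NAT or hide its benefit.

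**Working it through.** **Does the design already balance this contrast?** The RDD (Implementation, under allocation) uses thresholds at 13 and 36 and compares clients on either side of a threshold. Treated and waiting clients in row [1] both lie between the thresholds, so the RDD says nothing about their comparability. No queue order, random element or priority rule is stated.

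**Is there a figure to reproduce?** No. The article gives no event rate, allocation share or numeric power for 2a/2b. It gives only about 1,500 residents with 30–50% participation, that is 1,500 × 0.30 = 450 to 1,500 × 0.50 = 750 over all RHS groups. The yellow share is not given. Every rate and every n below is an assumption.

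**Crude risks with no NAT effect.** Take two equal language groups, A and B, with outcome risks pA = 10% and pB = 20% and shares treated eA = 80% and eB = 30%.

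- NAT: (eA·pA + eB·pB)/(eA + eB) = (0.08 + 0.06)/1.1 = 12.7%
- Waiting: ((1−eA)·pA + (1−eB)·pB)/(2 − eA − eB) = (0.02 + 0.14)/0.9 = 17.8%
- Ratio: 12.7/17.8 = 0.72

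With a milder imbalance (70% and 40% treated): 0.15/1.1 = 13.6% against 0.15/0.9 = 16.7%, ratio 0.82.

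If the better-served group has the higher risk (pA = 20%, pB = 10%, shares 80% and 30%), the sign turns: (0.16 + 0.03)/1.1 = 17.3% with NAT against (0.04 + 0.07)/0.9 = 12.2% waiting.

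**False rejection at nominal two-sided 5%** (simulation, 4,000 trials per setting, no NAT effect, risks 10% and 20%):

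| Shares treated | n = 200 | n = 300 | n = 400 | Stratified test |
|---|---|---|---|---|
| 80% / 30% | 17.8% | 24.5% | 29.5% | 4.4–5.0% |
| 70% / 40% | 9.3% | 11.7% | 13.2% | 4.9–5.2% |

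The normal approximation agrees. At n = 200 there are 110 NAT and 90 waiting clients with pooled risk 15%. The standard error is √(0.15 × 0.85 × (1/110 + 1/90)) = 0.051 and the spurious difference is 0.051, so the shift is about 1.0 standard errors and rejection about 17%. At n = 400 the shift is about 1.4 and rejection about 29%.

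**Wider range.** A second simulation (20,000 trials per setting; n = 180, 300, 450; shares treated from 60/40 to 80/20; risks 15/25 or 10/30) gave false rejection from 6.0% to 89.2% wherever both access and risk differed by group. A Cochran-Mantel-Haenszel test stratified by group stayed at 4.7–5.3%. Where either access or risk was equal across groups, the plain chi-squared test stayed at about 5%.

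**The case against.** A reader might infer that clients can be served only by a matched counsellor, and that the waiting list is therefore made up of under-staffed language groups. The article does not say this. The sentence on similar cultural background concerns the screening session. The goal that covers NAT delivery mentions counsellors without a matching rule, and nothing states how the waiting list forms. A client with no matched counsellor might never be screened, and so never join the list; that would be a coverage problem and not confounding of this contrast. These limits stand. Confounding needs groups that are all served, but with unequal capacity to treat.

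Nor do the documents give outcome risk by language group, so the bias is conditional and its size unknown. The range of 6.0% to 89.2% shows what can happen, not what will. The calculations cover the binary outcome only. For hypothesis 3 the mixed model uses repeated measures, so stable level differences between groups would not imitate an effect on change; different courses over time would be needed.

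The article also gives some ground of its own. Under analysis [3] it promises adjustment for confounders identified in advance, and the Limitations admit compromised randomisation and a heterogeneous population. A separate analysis plan may name covariates. But the adjustment sentence is not tied to 2a/2b and names no factor, and the Limitations disclose the problem without handling it. For 2a/2b the article itself commits to an unadjusted test and an empty mitigation cell. That is a stated choice and not detail left for later.

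**Conclusion.** The concern holds in conditional form. NAT versus awaiting NAT is a non-randomised comparison within one RHS band. No assignment rule is stated, the RDD gives no balance, Table 1 gives no mitigation, and the named test for 2a/2b is unadjusted. These points come directly from the article.

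Language or culture group is a plausible confounder grounded in the delivery model, but it is inferred. It biases the test only if access and outcome risk both differ by group, and it may act in either direction. As an illustration under assumed rates, 12.7% against 17.8% arises with no true effect, and the nominal 5% test rejects in roughly 18–29% of trials at n = 200–400, while stratification keeps about 5%. No size is claimed for this trial, and none for hypothesis 3. The change should be made because it is cheap and the stated test offers no protection.

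**What to change.** - Make the main analysis of 2a/2b a logistic regression adjusted for language/culture group and baseline RHS score, or a Cochran-Mantel-Haenszel test stratified by that group. Keep the chi-squared test as descriptive only.
- In the GLMM for comparator [1], add the group and its interaction with time as fixed effects.
- State how clients come to start NAT or to wait, and record the language/culture group and the counsellor for each client.
- In Table 1 row [1], name non-random selection as a limitation, enter the adjustment as the mitigation, and state that residual confounding remains.

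The cost is analysis wording and one variable that should be known from the assignment of the counsellor. Groups with only treated or only waiting clients add little or nothing to this contrast, which shrinks a comparison whose control group already has unknown size, and small groups may need pooling. Other possible drivers of waiting, such as arrival order, motivation or relocation, stay unadjusted, so the result remains observational.
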